**Fig. 1 Fig1:**
[figure not shown]
Study flow chart

In both arms of the study, patients will undergo a hepatectomy by open approach, with intraoperative measurement of portal vein and inferior vena cava pressures before and after liver resection. All patients will benefit from an abdominal drainage. Randomization will be performed after the abdomen is opened and any contraindication for resection (i.e. peritoneal carcinomatosis) has been precluded. Patients will be randomized in equal proportions in two groups. Patients in the experimental group will receive an intravenous postoperative infusion of somatostatin (Eumedica SA, Manage, Belgium) during 5 days at 6 mg/day, followed by one day at 3 mg/day. Treatment will be stopped at the end of day 6. Patients in the control group will receive a placebo infusion consisting of a daily 50 ml intravenous infusion of 0.9% NaCl during 6 days. No additional postoperative infusion or injection of somatostatin or any analogue of somatostatin will be performed during postoperative course.

In order to allow a double-blind design, preparation of somatostatin or placebo will be performed outside the ward where the patient is located by a pharmacist aware of the randomization results. The surgeons and nurses in charge will thus be unaware of the allocated treatment. Intraoperative management of vascular fluids and postoperative management of ascites will be defined by a common protocol. Abdominal drains will be left in place during at least 4 days and will be mobilized systematically from postoperative day 5 onwards.

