### Endpoints and outcome measurements

The primary endpoint will be the presence or absence of postoperative ascites occurring during the postoperative course (within 90 postoperative days). Postoperative ascites will be defined by the existence of ≥500 ml / 24 h of fluid in the drains during at least 3 days, or any ascites requiring an invasive procedure comprising percutaneous puncture or drainage (radiologically or surgically). This definition of ascites of ≥500 ml/24 h is the most common definition of postoperative ascites in the medical literature: several widely reported studies have used that definition [26–31]. Moreover, Azoulay et al. added to this definition the necessity of a 3-day period, which avoids selection bias related to postoperative fluid caused by bleeding, residual lavage or bile leakage [27]. In addition to this definition, we added the need for an invasive procedure as a definition of ascites because some patients may develop ascites after drain removal, or may develop some ascites that is not drained appropriately by the surgical drain, which will require additional invasive management such as puncture or drainage.

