Secondary endpoints are duration and total amount of ascites, postoperative overall 90-day morbidity, the existence and the severity of postoperative liver failure, the existence and the severity of postoperative acute renal failure, postoperative mortality (overall and liver-related), length of stay in intensive care unit, and length of hospital stay. A standardized definition and/or grading system will be considered for all these secondary endpoints as follows: duration of ascites will be defined as the number of days with ascites ≥500 ml/24 h; total amount of ascites will be defined as the total quantity of ascites collected by the drains from surgery to drain removal, associated with the total quantity of ascites collected by radiological puncture or drains if secondary drainage or puncture has been performed; postoperative morbidity will be graded according to the Dindo-Clavien scale [32]; postoperative liver failure will be defined and graded according to the International Study Group of Liver Surgery (ISGLS) definition and grading system [33]; postoperative acute renal failure will be defined according to the “Acute Dialysis Quality Initiative” (ADQI) definition and graded according to the “Risk, Injury, Failure, Loss, End-stage kidney disease” (RIFLE) Scale [34]; postoperative mortality will be defined as any death occurring within 90 postoperative days. Cases of death will be divided into liver failure-related versus liver failure-unrelated deaths.

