### Sample size and statistical analysis

The hypothesis of this phase III study is that the postoperative intravenous infusion of somatostatin during the 6 first postoperative days will reduce the rate of patients developing postoperative ascites. Based on previous published studies, the incidence of postoperative ascites in patients undergoing hepatectomy for HCC is estimated to be 35% (the reported incidence in literature varies between 5 and 56% [26–31], with a median value of 35%, which is consistent with our own experience of 33% postoperative ascites following hepatectomy by laparotomy for HCC at our institution [unpublished data]).

We postulate that we will observe a reduction of the incidence of postoperative ascites from 35% in the control arm to 15% in the experimental arm. In order to demonstrate a 20% difference with an alpha risk of 5% and a power of 80% using a two-tailed hypothesis, 72 patients in each arm will be necessary. Due to the short follow-up period of 90 days in this study, we assume that no more than 1 patient will be lost to follow-up. Additionally, we assume that 5% (*n* = 7) of the included patients will be precluded from surgical resection due to the findings of the surgical exploration (for instance, because of peritoneal carcinomatosis at surgical exploration), and thus will not be evaluable. Therefore, a total of 152 patients will have to be included in this study. To reach this number of patients, a 2-year inclusion period will be necessary.

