Patients included in this study will be analyzed on an intent-to-treat basis, and therefore kept in their initial treatment arm, even if the experimental treatment must be interrupted for any reason. The primary endpoint will be expressed in total number of cases in each group and in percentages with 95%-confidence interval. The secondary endpoints’ categorical variables (severity of ascites, postoperative morbidity, postoperative liver failure, postoperative acute renal failure, postoperative mortality) will also be expressed in total number of cases in each group and in percentages with 95%-confidence interval. These categorical variables will be compared between the two study arms using the chi-2 test or the Fisher’s exact test, as appropriate. The secondary endpoints’ continuous variables (duration of ascites, total amount of ascites, length of stay in intensive care unit, length of hospital stay) will be expressed as median values and range, and will be compared using the Mann-Whitney U-test. In order to take account of the potential effects of confounders on the primary endpoint, univariate and multivariate logistic regressions will be performed.

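### Early deaths count as absence of ascites and as short stays; the bias on the primary endpoint is probably small, but no planned analysis corrects for it

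*Protocol article*

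**What the plan says.** Under Endpoints and outcome measurements the protocol article states: "The primary endpoint will be the presence or absence of postoperative ascites occurring during the postoperative course (within 90 postoperative days"). There are two ways to meet it: high drain output on at least three days, or ascites that needs an invasive procedure. Death is not part of the definition.

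The same section defines duration of ascites as a count of days above the drain threshold, and total amount as the volume collected by drains and any later puncture or drainage. Mortality within 90 days is a separate secondary endpoint: "Cases of death will be divided into liver failure-related versus liver failure-unrelated deaths".

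Under Sample size and statistical analysis, patients are analysed by intention to treat. The four continuous secondary outcomes ("duration of ascites, total amount of ascites, length of stay in intensive care unit, length of hospital stay) will be expressed as median values and" …) are compared by Mann-Whitney test. Mortality is compared by chi-square or Fisher's exact test.

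That section also sets out who will not be evaluable. It says "we assume that no more than 1 patient will be lost to follow-up", allows for 7 patients found unresectable at exploration, and concludes that "a total of 152 patients will have to be included in this study". Deaths are in neither group.

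**The concern.** Death competes with ascites and with discharge. A patient who dies in the first days without a qualifying drain record or a procedure stays in the denominator, and a present/absent endpoint leaves only the value absent. If that patient dies in hospital, both lengths of stay end at death, and a rank test on raw days places them with the quickest recoveries.

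Such deaths may not be neutral. The Background ties ascites to portal hyperperfusion of a reduced liver remnant, and the endpoint section provides for liver-failure deaths. Patients at risk of early liver-failure death may therefore also be at raised risk of ascites. If one arm had more early deaths, it would gain on the primary endpoint, and on length of stay, for the wrong reason.

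**Working it through.** **Inputs from the article.** Ascites falls "from 35% in the control arm to 15% in the experimental arm"; "with an alpha risk of 5% and a power of 80% using a two-tailed hypothesis, 72 patients in each arm will be necessary"; "Patients will be randomized in equal proportions in two groups". No mortality rate is given, so every death count or rate below is an assumption.

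**1. The planned sample size.** With pooled variance under the null:

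n = [1.96·√(2·0.25·0.75) + 0.8416·√(0.35·0.65 + 0.15·0.85)]² / 0.20² = (1.200 + 0.501)² / 0.04 ≈ 72.4.

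This agrees with the stated 72; power at 72 per arm is 79.8%. The total is 2·72 + 1 + 7 = 152. The sum has no allowance for deaths, so the plan's own count treats patients who die as evaluable.

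**2. Shift per early death.** Let q be the chance that a patient who died early would otherwise have met an ascites criterion. Then k extra early deaths in one arm lower its observed rate by k·q/72.

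| Extra early deaths | q = 35% (planned control rate) | q = 100% (ceiling) |
|---|---|---|
| 1 | 0.35/72 = 0.5 points | 1/72 = 1.4 points |
| 3 | 1.05/72 = 1.5 points | 3/72 = 4.2 points |

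Against the planned 20 points, three deaths amount to 1.5/20 = 7% or, at the ceiling, 4.2/20 = 21%.

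**3. Chance of a false benefit on the primary endpoint.** Assume 35% ascites risk in both arms (no true effect), with all excess deaths in the somatostatin arm and before ascites could be recorded. The nominal chance of significance in favour of somatostatin is 2.5%.

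| Excess early mortality | q = 35% | q = 100% |
|---|---|---|
| 2 points (1.4 of 72) | 3.1% | 4.4% |
| 5 points (3.6 of 72) | 4.1% | 9.3% |
| 10 points (7.2 of 72) | 6.5% | 25.6% |

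In counts, against 25/72 in control, 14/72 gives chi-square p = 0.039, 15/72 gives 0.063 and 16/72 gives 0.097. Fisher's test needs 13/72 (p = 0.037). Starting from equality, 11 to 12 ascites events would have to be masked to reach significance. Near the boundary, one or two are enough.

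**4. Length of stay.** Illustrative simulation: 72 per arm, lognormal stay with median 10 days and log-SD 0.5, no true difference, excess in-hospital deaths in the somatostatin arm. The stay distribution is also an assumption.

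| Excess deaths | Early deaths (stay 1–7 days): false shorter stay | Late deaths (stay 10–60 days): false longer stay |
|---|---|---|
| 2% | 3.6% | 3.9% |
| 5% | 6.0% | 6.1% |
| 10% | 13.9% | 13.7% |

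The distortion is about equal in size and opposite in direction, depending on when the deaths occur.

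**The case against.** The strongest reply is that the article nowhere says that early deaths are scored as successes. It is a condensed report, and a rule for deaths may sit in the full protocol or analysis plan. It is true that no such rule is written, and a reader should not infer that the trialists chose this scoring. The point rests on something narrower: a present/absent endpoint, intention-to-treat analysis, rank tests on raw stays, and a count of non-evaluable patients that leaves out deaths. Applied as published, these give the result described.

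A reader might also infer that excess deaths in an arm would look like benefit on the primary endpoint and on all four continuous outcomes. The documents do not support that:

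- A patient who meets either criterion and then dies is still an event. Drain output is recorded every 8 hours and drains stay in for at least 4 days, so the drain criterion can be met by about day 3, and the procedure criterion has no minimum duration.
- Death after a long stay lengthens stay. Death after prolonged ascites adds days and volume.

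Finally, excess deaths would not be hidden, because 90-day mortality is compared between arms. That is right, but the comparison leaves the ascites and stay results as they are, and it is insensitive at this size: 3 versus 0 deaths in 72 per arm gives Fisher p = 0.24.

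**Conclusion.** The point holds for deaths before ascites is recorded and, for stay, for early in-hospital deaths. As defined, the first count as absence of ascites and the second rank as favourable. Late in-hospital deaths bias the stay comparison the other way.

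On the primary endpoint the bias is probably a point or two. Three extra early deaths give about 1.5 points at the protocol's own 35% risk. The 4.2-point figure is a ceiling that requires every one of those patients to have been going to develop ascites. A large distortion needs about 10 points of excess early mortality falling almost entirely on such patients, and nothing in the documents suggests that. The issue is therefore worth settling in the analysis wording, but it does not undermine the choice of primary endpoint. All sizes rest on assumed deaths, and the stay results also on an assumed distribution.

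**What to change.** - **Primary endpoint:** keep it and its planned test. Add one prespecified sensitivity analysis that counts ascites or death by day 90 as failure.
- **Intensive care and hospital stay:** give in-hospital deaths the worst rank in the Mann-Whitney test, or analyse time to discharge alive. Show mortality and survivor medians beside the result.
- **Duration and volume of ascites:** no worst-rank rule is proposed. It would score a death unrelated to the liver as the heaviest ascites.

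The cost is wording fixed before unblinding. Deaths to day 90 are already collected, and planned power is untouched because the composite does not become primary. It would have less power as a stand-alone test. With equal mortality of 2%, 5% or 10% in both arms, independent of ascites (assumed), the rates become 36.3% v 16.7%, 38.3% v 19.3% and 41.5% v 23.5%, and power at 72 per arm is 76.5%, 71.6% and 63.8%. It should therefore be read for consistency of the estimate, not for its own p-value. The other downside is that the stay comparison then mixes survival with stay, which is why mortality and survivor medians belong beside it.

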### Ethical considerations and written informed consent

The present study protocol was approved by the Institutional Review Board, the French National Agency for Medicines and Health on the 11 of July 2017 under the registration number 170335A-42, and the “Est II” ethic committee on the 11 of September 2017, under the registration number EudraCT2016–004230-20. The institutional promoter is the University Hospital of Lyon (Hospices Civils de Lyon), France. The trial has been registered on the ClincialTrials.gov website under the identification number NCT02799212. This study received a grant from the French National Cancer Institute in January 2016 (Grant reference number: PHRC-K15–103).

A written informed consent will be obtained from each participating patient before inclusion to the study. The appropriate time to inform the patient about the study (before or after the board meeting) is left to the medical team’s discretion. The patient will be given a minimum period of 1 week to consider the project before signing the written inform consent. The written inform consent form signed by the patient is obtained by the local investigator the day prior to surgery as patients are hospitalized at least one day before surgery. The head of each team will be the local investigator of each participating center and will be responsible for patients’ information, inclusion and follow-up. Each investigator shall undertake to fulfill the obligations of the law and to conduct research according to Good Clinical Practice guidelines, in accordance with the terms of the Declaration of Helsinki.

## Discussion

Surgical resection represents the only chance for cure for most patients presenting with early stage HCC and not eligible for liver transplantation. Unfortunately, most patients developing HCC also suffer from underlying liver disease, which exposes them to the risk of postoperative ascites and subsequent severe morbidity. Currently, the means to prevent postoperative ascites and post hepatectomy liver failure are mainly prophylactic, including preoperative management of diabetes, malnutrition, cardiorespiratory disease, preoperative optimization of the future liver remnant by contralateral portal vein embolization and biliary drainage in case of cholestasis. In addition to those prophylactic means, some authors have proposed to perform concomitant surgical portal inflow modulation in association to hepatectomy, either by splenic artery ligation or splenectomy [13–15, 39], but those techniques are invasive, irreversible and quite risky, especially in patients with underlying liver disease.

Somatostatin is a well-known drug already used in several indications, including pancreatic fistula, upper gastrointestinal bleeding, acromegaly, and endocrine tumors, with considerable long-term experience. Treatment dosage and duration that may be used in the present study are the same than those already used in upper gastrointestinal hemorrhage related to variceal bleeding, as this configuration allows a significant decrease in portal pressure [20].

The present study represents the first randomized controlled trial to assess the benefits of somatostatin on the risk of postoperative ascites after surgery for HCC. If the efficacy of somatostatin in preventing postoperative ascites is demonstrated, it would represent a novel and original therapy that would increase the safety of hepatectomy for HCC in patients with underlying liver disease in a context where hepatectomy remains the best curative therapeutic option in patients unsuitable for liver transplantation.

## Abbreviations

ADQI: Acute dialysis quality initiative
CT: Computed tomography
HCC: Hepatocellular carcinoma
ISGLS: International study group on liver surgery
RIFLE: Risk, injury, failure, loss, end-stage;
